#### 2.3.5. Relevant concomitant care and interventions.

If concomitant medication or treatment within the last 3 months that could potentially affect CLBP is identified during screening, a wash-out period of at least 2 weeks is required before proceeding. There are no relevant concomitant care or interventions permitted during the study.

### 2.4. Primary and secondary endpoints

The primary endpoint is 2 weeks after treatment compared to baseline (visit 1). The secondary endpoints are presented in Table 2.

**Table 2 T2:** Secondary outcomes.

Assessment method	Objective	Endpoint
Shear wave elastography	To assess the efficacy of Moving cupping therapy	3 wk after baseline (1 wk post-treatment)
NRS	To assess the efficacy of Moving cupping therapy	3 wk after baseline (1 wk post-treatment)
ODI	To assess the efficacy of Moving cupping therapy	3 wk after baseline (1 wk post-treatment)
EQ-5D	To assess the efficacy of Moving cupping therapy	3 wk after baseline (1 wk post-treatment)
PGA	To assess the efficacy of Moving cupping therapy	3 wk after baseline (1 wk post-treatment)
Outlier detection	To assess the efficacy of Moving cupping therapy and reflect the psychological state of participating patients in the study	Visit 4 (twice a wk visit, 2 wk)
BMI	To evaluate the impact of obesity on Moving cupping therapy	Screening phase

BMI = body mass index, NRS = numeric rating scale, ODI = Oswestry disability index, PGA = patient global assessment.

### 2.5. Data collection and management

An electronically generated Case Report Form will be used and managed by qualified and authorized investigators and physicians. All the data recorded in the electronically generated Case Report Form will be consistent with those of the original material. During the study, the investigator will collect data at each visit. All study findings and records will be treated with strict confidentiality, and patients are to be identified solely by their patient number and/or birth date, and never by name. To protect participant anonymity, the investigator will maintain the confidentiality of the patient-identifying documents. The following data will be collected.

Date of birth (age), sex, medical history, history of current disease, and pregnancy status.Body weight and height at first visit, including BMI calculations.Vital signs (body temperature [°C], blood pressure [mm Hg], pulse rate [beats/minute]) at every visit.SWE before and after each treatment.NRS score at screening and visits 1, 4, and 5.Oswestry Disability Index and EQ-5D index at visits 1, 4, and 5.Patient Global Assessment at screening visits, and visits 1, 4, and 5.Outlier detection for each procedure.

Additionally, an independent clinical research organization will conduct data management and data monitoring. Interim analyses will not be conducted, and the trial will be terminated by the principal investigator when the study process for all enrolled study participants has been completed.

### 2.6. Statistical analyses

The population to be analyzed is defined as all intervention and control groups that participate in the moving cupping study. Descriptive statistics will be used to summarize the demographic characteristics and baseline clinical data of the participants, including variables such as sex, age, BMI, medical history, and medication history by treatment group. All statistical analyses will be 2-tailed, with a significance level of 5%. Statistical software SAS Version 9.4 (SAS Institute, Inc., Cary, NC) will be used for the analysis. In the case of missing values, multiple imputations will be used for data processing.

## 3. Discussion

Previous studies on Korean medicine have predominantly relied on subjective measures for assessing treatment efficacy, limiting their ability to provide objective information on changes before and after treatment.^[14]^ To address this limitation, we used SWE in our protocol for evaluating the efficacy and safety of moving cupping combined with SWE for CLBP management. This approach allowed us to quantify changes in muscle stiffness as an objective measure of the therapeutic benefits of moving cupping. Our study is unique in that it evaluates the effectiveness of moving cupping in promoting muscle relaxation, pain relief, and healing through SWE, providing a novel approach to CLBP management. Additionally, the use of SWE in measuring muscle stiffness changes is a significant departure from previous Korean medicine studies, which primarily relied on subjective assessments.

In this study, we outlined a protocol for an RCT aimed at evaluating the efficacy and safety of moving cupping combined with SWE for CLBP management. The use of objective measures to assess complementary therapies is a significant challenge in the field, and this study aimed to address this issue by using SWE to assess muscle stiffness and relaxation as a quantitative measure of the therapeutic benefits of moving cupping.

As previously suggested, the degree of muscle contraction in the lower spine may vary depending on the underlying condition causing the low back pain, such as a herniated disc.^[15]^ Furthermore, CLBP and muscle stiffness are interrelated, with muscle stiffness being both a cause and consequence of CLBP.^[16]^

The use of this RCT protocol has the potential to significantly improve our understanding of the efficacy of moving cupping as a complementary therapy for managing CLBP and other musculoskeletal conditions. The findings may provide valuable insights for clinicians and researchers to optimize the clinical application of moving cupping and SWE in managing CLBP, potentially improving patient outcomes and quality of life.

This RCT protocol has several limitations. First, it is not double-blinded, which may introduce researcher bias. However, the protocol minimizes bias by taking the mean of 10 out of the 12 quantitative values recorded in ultrasound images and excluding the maximum/minimum values. Second, it is not an absolute comparison study, and variance may be high owing to individual differences in values. However, it evaluates the effectiveness of recovery through a relative value comparison before and after treatment, and explores the significance of value changes with qualitative evaluations such as the NRS. Third, it is a placebo-controlled study, and information bias may be introduced if the patient understands the difference in treatment. However, it controls for participants’ expectations by excluding those who have experienced moving cupping, omitting treatment information, or offering a sham treatment similar to the actual procedure.

There are several areas that warrant further research to determine the full scope and implications of this treatment. Long-term research on the efficacy of moving cupping and SWE in treating CLBP may provide additional insight into the potential for relieving and preventing symptoms. Additionally, exploring the therapeutic efficacy of this combined therapy for other conditions may open up new avenues for treating other diseases. Moreover, studying the combined therapy of moving cupping and SWE with other treatments may help identify the most effective approach to managing pain and improving function. Finally, providing clinical guidelines for the application of the RCT results may help healthcare professionals use this therapy more effectively to benefit their patients.

In conclusion, we present a RCT protocol for investigating the efficacy and safety of moving cupping combined with SWE for patients with CLBP. This therapy may have a significant effect on pain reduction and functional improvement. Such research avenues can expand our understanding of the potential benefits of moving cupping and SWE, and help optimize their clinical application.

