### 2.2. Study design and population

This study aims to investigate the efficacy and safety of moving cupping therapy for chronic pain using a parallel-arm RCT. The target population will consist of patients with CLBP who have experienced pain for at least 12 weeks. The study will be conducted at the outpatient clinics of the Pusan National University Hospital and Korean Medicine Hospital.

To ensure blinding, the study will include only patients with CLBP who have no prior experience with moving cupping. The study will be conducted by independent practitioners, with one performing the moving cupping treatment and the other evaluating SWE independently. Each treatment will be administered 4 times (twice a week, for 2 weeks), and a follow-up evaluation will be conducted 1 week later.

This study was designed as a superiority trial with a level of significance set at α = 0.05, a type II error (β) of 0.2, and a power of the test of 80%. The sample size was calculated based on similar studies,^[7]^ with a 1:1 ratio between the intervention and control groups, and a dropout rate of 15% was considered in each group. Sixty-eight patients with CLBP will be randomly assigned to either the intervention or control group in sealed envelopes. After treatment, patients will undergo an evaluation.

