#### 2.2.4. Study protocol.

Table 1 presents the comprehensive study schedule. Each candidate will receive an explanation of the study protocol from a physician and is required to provide consent. Thereafter, they will be requested to sign an informed consent form before proceeding with the examination, as shown in Table 1. To allocate enrolled study participants to either the treatment or placebo group during visit 1, independent researchers will deliver sealed and opaque envelopes labeled consecutively with numbers, which have been randomly allocated by an independent statistician. The blinding will be maintained until submission of the paper. Before and after each treatment session, SWE will be conducted. Additionally, the physician will monitor the adverse events during each visit.

**Table 1 T1:** Study schedule.

		Treatment phase				Follow-up phase
		1 wk		2 wk		3 wk
	Screening	Visit 1	Visit 2	Visit 3	Visit 4	Visit 5
Informed consent acquisition	√					
Confirmation of eligibility (inclusion and exclusion criteria)	√					
Vital signs measurement	√	√	√	√	√	√
BMI measurement	√					
Demographic survey	√					
Medical history survey for the back and other organs	√					
Clinical examination†	√					
Physical examination	√					
Random allocation		√				
Moving cupping		√	√	√	√	
Placebo		√	√	√	√	
Outlier detection		√	√	√	√	
Confirmation of concomitant therapy		√	√	√	√	√
Shear wave elastography (before)		√	√	√	√	
Shear wave elastography (after)		√	√	√	√	
Numeric rating scale (NRS)	√	√			√	√
Oswestry disability index (ODI)		√			√	√
EQ-5D index		√			√	√
Patient global assessment (PGA)					√	√
Adverse event monitoring		√	√	√	√	√
Dropout confirmation		√	√	√	√	√

BMI = body mass index.

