#### 2.3.3. Shear-wave elastography measurement.

After measurement by the evaluator using ultrasound equipment, all SWE images will be stored on a separate storage device by a different researcher. To analyze the images, a Q-box will be inserted into the SWE image to evaluate the mean shear modulus in kPa of all the muscle fibers within the region of interest. The Q-box spatially averages the propagation speed of each shear wave to determine the shear modulus of each area of the imaged tissue. The shear modulus values will be averaged for the selected tissue area by averaging all the shear modulus values. Once the appropriate Q-box position is determined, the shear modulus values will be recorded 12 times in each trial. To reduce bias, the maximum and minimum values of the 12 recorded shear modulus (kPa) values will be excluded, and the average of the remaining 10 values recorded.

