#### 2.3.4. Adverse events.

Possible adverse effects related to moving cupping include local adverse reactions such as blister formation, bleeding, persistent bruising, ongoing pain, stiffness, burning sensation, and heat at the treatment site. All significant adverse events that occur between the time of signing the informed consent form and the end of the trial will be documented in the medical records and reported to the Clinical Research Review Committee.

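### Dropping the highest and lowest of 12 elastography readings controls outliers; it does not reduce researcher bias from incomplete blinding, as the protocol claims

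*Protocol article*

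**What the plan says.** Section 3 (Discussion), in the limitations, states: "First, it is not double-blinded, which may introduce researcher bias". The next sentence offers the remedy: "the protocol minimizes bias by taking the mean of 10 out of the 12 quantitative values recorded in ultrasound images", with the maximum and minimum left out. Section 2.3.3 gives the same rule in the Methods and also describes it as a way to reduce bias.

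Section 2.3.3 also fixes the order of events: "Once the appropriate Q-box position is determined, the shear modulus values will be recorded 12 times in each trial". The placement comes first and the 12 readings follow from it.

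Other parts of the article bear on blinding:

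- Section 2.2 has one practitioner treat and another evaluate SWE independently.
- Section 2.3.3 has a different researcher store the images on a separate device.
- Section 2.2.4 describes sealed, opaque, numbered envelopes with an allocation drawn up by an independent statistician, and adds: "The blinding will be maintained until submission of the paper". It does not say whose blinding is meant.
- Sections 2.3.1 and 2.3.2 set suction at 18 to 20 kPa in one arm and 0 kPa in the other, with SWE after a 15-minute rest.
- Section 2.3.4 lists "blister formation, bleeding, persistent bruising" among the possible local reactions.

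**The concern.** The article names a specific risk, researcher bias from incomplete blinding, and then a specific safeguard. The safeguard belongs to a different problem. Trimming guards against a stray reading. It does nothing about a reader whose choice of Q-box position moves the whole set of readings in one arm relative to the other.

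This matters because the case for the trial rests on SWE being objective where pain scores are not (Introduction and Discussion). If the reader can know the arm, or whether an image is from before or after treatment, that advantage is weakened for the outcome it is meant to protect. A reader of the article would also be wrongly reassured that the risk had been handled.

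**Working it through.** **1. What trimming does to a shared shift.** Let x1 to x12 be the readings from one session. The recorded value is

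T = (sum of the 12 − maximum − minimum) / 10.

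Add the same amount c to every reading, as a displaced Q-box would:

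T′ = (sum + 12c − (maximum + c) − (minimum + c)) / 10 = T + 10c/10 = T + c.

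The shift passes through in full for any c and any distribution of readings. A simulation of 200,000 sessions with normal within-session error agrees: shifts of 0.5, 1 and 2 within-session SD appear as 0.50, 1.00 and 2.00 both in the plain mean of 12 and in the trimmed mean.

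**2. What trimming does achieve.** Results from the same simulation, with bias in within-session SD:

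| Disturbance | Plain mean of 12 | Trimmed mean |
|---|---|---|
| 1 reading off by 10 SD | 0.83 (= 10/12) | 0.16 |
| 3 readings off by 2 SD | 0.50 (= 3 × 2/12) | 0.46 |
| 6 readings off by 2 SD | 1.00 (= 6 × 2/12) | 1.00 |
| all 12 off by 2 SD | 2.00 | 2.00 |

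Trimming is useful against one wild value, and its benefit disappears as the disturbance becomes shared.

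**3. What a shared shift could do to the test.** Inputs from the article are 68 patients allocated 1:1, so 34 per arm; 15% dropout (section 2.2); and a two-sided 5% test (section 2.6). Evaluable per arm: 34 × 0.85 = 28.9, taken as 29. The sample size itself cannot be reproduced, because the article gives neither an effect size nor an SD. Nothing below depends on reproducing it.

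Assumptions: no true effect; a two-sample t test on the SWE outcome; and a reading shift of b between-patient SD in one arm relative to the other. The article gives no value for b, so a range is shown. The noncentrality is b × √(n/2), the degrees of freedom are 2n − 2, and for n = 29 the critical value is 2.003.

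| Assumed b | Noncentrality, n = 29 | False positives, 29 per arm | False positives, 34 per arm |
|---|---|---|---|
| 0 | 0 | 5% | 5% |
| 0.1 | 0.1 × √14.5 = 0.38 | 6.6% | 6.9% |
| 0.25 | 0.25 × √14.5 = 0.95 | 15.5% | 17.4% |
| 0.5 | 0.5 × √14.5 = 1.90 | 46.5% | 52.9% |

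**4. Whether trimming lowers these rates.** Simulated trials with 29 per arm, and within-session SD assumed to be half the between-patient SD, gave these rejection rates with and without trimming: 0.116 and 0.115 at b = 0.2; 0.203 and 0.204 at b = 0.3; 0.459 and 0.459 at b = 0.5. The differences are simulation noise.

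**The case against.** Several stronger readings are tempting, and the article does not support them.

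- *The SWE evaluator is unblinded.* The article says only that the trial is not double-blinded. With suction at 18 to 20 kPa against 0 kPa the therapist cannot be blinded, and the phrase may mean no more than that. The evaluator is named as independent. Skin marks are listed only as possible reactions, with no frequency, so nothing shows how often the arm could be guessed. The route to unmasking is plausible but not demonstrated.
- *The person who sees the skin places the Q-box.* Section 2.3.3 has the Q-box inserted into the SWE image for analysis and does not say that the scanner does it. Nor does the article say whether the scan before or after treatment at visit 4 feeds the primary comparison; the scan before treatment is not taken 15 minutes after suction.
- *The two blinding statements contradict each other.* They can be reconciled if some people are blinded and the therapist is not. They are unclear together, because neither says who is blinded.
- *Trimming is the only safeguard.* It is not: role separation, separate image storage and concealed allocation are all stated. None of them is stated to mask the reader.
- *The false-positive rate will be 46%.* That figure belongs to an assumed shift of 0.5 SD. At 0.1 SD it is under 7%. The direction of any bias is also not established.

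It is also fair to say that the authors disclose the limitation themselves, and that image-coding procedures may sit in a fuller protocol. That answers a charge of omission. It does not answer the point made here, which is that the article puts forward trimming as the remedy for researcher bias, and trimming is not one.

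**Conclusion.** The claim that trimming minimises researcher bias is wrong as written, in section 3 and in the shorter form in section 2.3.3. The algebra needs no assumption about the size of the bias: a shift common to all 12 readings is reduced by 0%. It does rest on the 12 readings sharing one Q-box position, which is how section 2.3.3 describes them.

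The effect on the trial's conclusions is conditional. It requires a reading bias that differs between arms, and the rates of about 7%, 15% and 46% follow from assumed shifts of 0.1, 0.25 and 0.5 SD with 29 per arm. It also takes SWE to be the primary measure; section 2.4 gives the time point without naming the measure, and SWE is inferred from the title and aims.

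This should be fixed. The rationale is wrong and a cheap safeguard is within reach, but actual bias has not been shown and no design figure changes.

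**What to change.** In section 2.3.3:

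- The researcher who already stores the images replaces patient, arm, visit and before/after labels with random codes and shuffles the order.
- Existing study staff who do not know the allocation, and not the therapist, place the Q-box and take the 12 readings from the coded images.
- The codes are unlinked only after database lock.

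In sections 2.3.3 and 3, keep the trimming rule but describe it as outlier control, and delete the claim that it deals with the lack of double-blinding. State who is blinded (patient, therapist, scanner, image reader, analyst) so that sections 2.2.4 and 3 agree. Cite the separate therapist and evaluator, and the separate image storage, as the safeguards they are.

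Acknowledge what remains: coded reading protects Q-box placement and reading, not image acquisition, where the person scanning may see skin marks.

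The cost is a file-coding step by someone already named in the plan, and readings are no longer available on the day of the visit. Treatment, visits and sample size do not change.

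### The article describes its efficacy comparison only as a relative before/after value; a between-arm ANCOVA adjusted for Visit 1 stiffness would state the contrast and be more efficient at no cost

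*Protocol article*

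**What the plan says.** Section 2.2 sets the design: "This study was designed as a superiority trial with a level of significance set at α = 0.05", 80% power, 1:1 allocation, 15% dropout per group and 68 patients. Section 2.3.2 gives the control arm the same procedure at 0 kPa.

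The efficacy comparison itself is worded only in before/after terms:

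- Section 2.4 gives the primary endpoint as "2 weeks after treatment compared to baseline (visit 1" and names neither a variable nor a contrast between arms.
- The limitations paragraph in section 3 disclaims an absolute comparison and concedes that "variance may be high owing to individual differences in values". As the answer, it says that "it evaluates the effectiveness of recovery through a relative value comparison before and after treatment".
- The Discussion part of the abstract likewise speaks of relative comparisons before and after treatment.

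Section 2.6 covers the analysis population, descriptive summaries by group, two-tailed testing at 5%, the software and multiple imputation. It does not alter the before/after wording. Table 1 schedules SWE before and after each of the four treatment sessions, and NRS, ODI and EQ-5D at Visits 1, 4 and 5.

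**The concern.** The article gives a statistical reason for its choice: patients differ widely in stiffness, so each is compared with their own baseline as a relative value. That reasoning can be checked, and it is weak.

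Subtracting baseline removes between-person variance only to the extent that baseline and follow-up correlate, and it adds the baseline's own noise. Dividing by baseline adds further noise when baselines vary widely, which is the situation the article describes. Regression on baseline uses the same information with the best-fitting slope, so for large samples it is never less precise than the change score.

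A trial with about 29 evaluable patients per arm has little power to spare. The wording also leaves the reader to infer the contrast that a sham-controlled superiority trial needs.

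**Working it through.** **Inputs from the article.** Two-sided alpha 0.05, power 80%, 1:1 allocation, 15% dropout, 68 in total (sections 2.2 and 2.6). No effect size, SD or sizing outcome is stated, so 68 cannot be reproduced forward.

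**Inputs assumed.** The correlation r between Visit 1 and Visit 4 stiffness, and the baseline coefficient of variation (CV). Neither is in the article, so ranges are shown.

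**Back-solving the sample size.** 29 × 1.15 = 33.35, rounded up to 34 per arm, or 68. (Dividing by 0.85 instead gives 34.1, rounded up to 35 per arm, or 70.) About 29 evaluable per arm is therefore consistent with the plan. The implied standardised difference is

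d = (1.960 + 0.842) × √(2/29) = 0.736,

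or 0.75 from the t distribution.

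**Variance of the between-arm contrast,** relative to the follow-up variance:

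- follow-up only: 1
- change score: 2(1 − r)
- ANCOVA: 1 − r²

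The ratio of ANCOVA to change score is (1 + r)/2, that is 0.65, 0.75 and 0.85 at r = 0.3, 0.5 and 0.7.

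**Power** = Φ(2.802/s − 1.960), where s is the square root of the relevant variance factor and 2.802 = d/√(2/29). For r = 0.3:

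- change score: s = √1.4 = 1.183, so Φ(0.408) = 65.8%
- ANCOVA: s = √0.91 = 0.954, so Φ(0.977) = 83.6%

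| r | Follow-up only | Change score | ANCOVA |
|---|---|---|---|
| 0.3 | 80.0% | 65.8% | 83.6% |
| 0.5 | 80.0% | 80.0% | 89.9% |
| 0.7 | 80.0% | 95.1% | 97.5% |
| 0.8 | 80.0% | 99.3% | 99.7% |

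**If the effect was instead specified on the change-score SD,** the change score has its 80% by construction. ANCOVA then gives 93.5%, 89.9%, 86.0% and 82.0% at r = 0.3, 0.5, 0.7 and 0.9.

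**Percent change,** if that is what the relative value means. These are 20,000 simulated trials per setting, 29 per arm, d = 0.736, with t-based tests, so the figures sit slightly below the formula values:

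| r | Baseline CV | Percent change | Change score | ANCOVA |
|---|---|---|---|---|
| 0.3 | 0.2 | 62.0% | 64.2% | 81.4% |
| 0.3 | 0.3 | 53.3% | 64.7% | 81.1% |
| 0.5 | 0.2 | 77.9% | 79.1% | 88.2% |
| 0.5 | 0.3 | 69.6% | 78.7% | 88.4% |
| 0.7 | 0.2 | 94.4% | 94.7% | 96.9% |
| 0.7 | 0.3 | 90.1% | 94.5% | 96.8% |

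Percent change never beats the change score here and falls further behind as the CV rises. At r = 0.3 it is also well below the 80% of a follow-up-only comparison. With no true difference, all three between-arm tests rejected in about 5% of simulated trials, so each is valid; they differ in efficiency.

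**The case against.** The limitations sentence describes an outcome metric, not a test. In a parallel-arm, sham-controlled superiority trial, its natural meaning is change from each patient's own baseline, compared between arms. That is a legitimate analysis. The model and its covariates may well be in a full protocol or analysis plan that is not shown, so their absence from a condensed article is no fault. This stands.

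The size of the gain is also conditional. At r = 0.5 the change score already reaches the planned 80%, and above 0.5 it beats a follow-up-only comparison. At r of 0.8 or more, ANCOVA adds almost nothing. This stands too.

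A reader might infer something stronger: that each arm will be tested only against its own baseline, so that efficacy could be claimed when the cupping arm changes significantly and the sham arm does not. That rule would be unsound. In simulation with two identical arms and a shared 0.3 SD improvement, it would be met in 22% to 25% of trials (r = 0.5 and 0.7). But the article nowhere states such a rule, nor that the arms will not be compared, so this figure does not describe the plan. Nor can it be said that the analysis departs from what the trial was sized for, because the sizing outcome and effect are not given.

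What remains is that the article does state a method and a reason for it. The reason does not hold reliably, and a better method needs no further data.

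**Conclusion.** The point holds as a recommendation on efficiency and clarity. The article words its comparison only as before/after and offers a relative value as the remedy for high variance. Compared between arms, that value gives a valid test, but one with less power than baseline-adjusted ANCOVA: about 18 percentage points less for the change score at r = 0.3, 10 at r = 0.5, 2 at r = 0.7 and under 1 at r = 0.8. The loss is larger for percent change when the baseline CV is high.

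These sizes rest on 29 evaluable patients per arm, d of about 0.74 to 0.75 on the follow-up SD, and assumed values of r and CV. The direction does not depend on those values as long as r is below 1. The verdict also takes SWE stiffness as the primary variable and Visit 4 as its time point, as the aim and abstract suggest, although section 2.4 names neither. The documents do not show an invalid test.

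**What to change.** State in sections 2.4 and 2.6 that:

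- The primary analysis compares the arms on Visit 4 shear modulus by ANCOVA, with arm as factor and Visit 1 pre-session shear modulus as covariate.
- The outcome is either the pre-session or the post-session reading at Visit 4. Table 1 schedules both, so one must be named.
- If a relative effect is wanted, both shear modulus values are log-transformed and the result is reported as a ratio of geometric means with a 95% confidence interval.
- NRS, ODI and EQ-5D are analysed in the same way, each adjusted for its own Visit 1 value.
- Within-arm changes are reported descriptively only.

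Then reword the limitations sentence in section 3 to match: individual differences in stiffness are handled by adjusting for baseline in the between-arm comparison.

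The cost is wording and one standard model in SAS. All the Visit 1 values are already collected, and neither visits nor sample size change. The choice should be fixed before the data are unblinded.
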